### **Demonstrate the technical merit of the application (Criterion 3)**

#### **Study design**

The proposed study will use a randomized clinical trial design to *compare the effectiveness* of 1) traditional smoking cessation (SC) versus 2) long-term, guided maintenance treatment with NRT (LT-NRT). Participants in the SSC arm (n=199) who are interested in quitting smoking the next 30 days will be offered 5 sessions of smoking cessation counseling over 12 weeks, supplemented with 10 weeks of combined NRT (patch plus choice of gum or lozenge). Participants in the LT-NRT arm (n=199) will receive 7 sessions of counseling extended over an entire year, focused on medication adherence and smoking reduction plus 52 weeks of combined NRT. Outcomes will be measured at 3, 6, and 12 months post randomization and will assess rates of smoking cessation, number of cigarettes smoked, tobacco smoke exposure, and clinical outcomes. In addition to comparing the effectiveness of treatment, a classification and regression tree analysis will allow us to identify subgroups of patients most likely to benefit from treatment.

### Study site

This study will be conducted at the Kansas University Medical Center (KUMC) and will take advantage of the infrastructure of the UKanQuit smoking cessation program. KUMC is an ideal setting for the conduct of this study. KUMC boasts a research participant registry and an electronic medical record (EMR) with an I2B2 research interface that will facilitate recruitment of participants. The smokers seen at KUMC come from urban and rural locations throughout Kansas, but mostly from Kansas City, Missouri and Wyandotte County, Kansas. (Wyandotte County is a majority minority county that has the dubious distinction of being one of the most disadvantaged jurisdictions in Kansas.) Our study site will allow us to enroll a diverse population of smokers for this study, including African American and Latino smokers with COPD. The experienced researchers in the UKanQuit program have an outstanding track record for recruitment of high risk smokers into clinical studies, recently enrolling more than 1,000 hospitalized smokers into an NIH-funded study designed to enhance utilization of tobacco quit lines.

### Participants

**Recruitment.** As part of the Frontiers Clinical and Translational Research program at KUMC, we recently established a research registry that now contains 303 smokers with COPD that have already agreed to be contacted for studies such as this one; this registry is increasing in size daily. We will also recruit from the more than 1,500 smokers with COPD seen each year in the KUMC clinics and hospital. Recruitment of these smokers is enhanced by the use of a real-time, required field in the electronic medical record that identifies smokers when they are first seen. An automated referral system sends a daily list of newly identified smokers to our team of tobacco treatment specialists who can then approach patients about participation in this study. We will also recruit from Swope Health Services, Inc., a Federally Qualified Health Center that has helped us recruit more than 1,500 African American smokers to 4 NIH-funded trials. In the unlikely event that we are

unable to recruit sufficient patients quickly enough at KUMC and Swope, we will extend recruitment to the Midwest Cancer Alliance – hospitals affiliated with the KU Cancer Center, that have helped us recruit almost 1,000 smokers for two other NIH-funded smoking cessation studies, other local pulmonary practices or community venues providing services to smokers.

**Eligibility.** Patients will be eligible for enrollment in this study if they are 18 years of age or older, have physician-diagnosed COPD, smoke 5 or more cigarettes per day, have smoked 25 of the past 30 days (not including days spent in the hospital), and speak either English or Spanish. (Table 1) Patients will be eligible

Table 1. Summary of inclusion and exclusion criteria

| Inclusion Criteria                                                                                                                                                                                                                                                                                                                                                        | Exclusion Criteria                                                                                                                                                                                                                                                                                                                               |
|---------------------------------------------------------------------------------------------------------------------------------------------------------------------------------------------------------------------------------------------------------------------------------------------------------------------------------------------------------------------------|--------------------------------------------------------------------------------------------------------------------------------------------------------------------------------------------------------------------------------------------------------------------------------------------------------------------------------------------------|
| 
 
• Aged 18 years or older
 
• Physician-diagnosed COPD
 
• Smoke <math>\geq 5</math> cigarettes/day
 
• Smoke cigarettes on <math>\geq 25</math> of the last 30 days
 
• Speak either English or Spanish
 
• Willing to take NRT for up to 1 year and participate in study procedures
 
 | 
 
• Reside in a facility that doesn't allow smoking
 
• Don't have an address and telephone
 
• Unstable cardiac condition (e.g. unstable angina or AMI in past 30 days)
 
• Pregnant or breast feeding
 
• Terminal illness with less than 12 month life expectancy
 
 |

regardless of their interest in quitting as long as they are willing to take NRT. Patients will be excluded if they reside in a facility that doesn't allow smoking (e.g. certain nursing homes), lack access to a telephone, are suffering from a terminal illness with a less than 12 month life expectancy, or have an unstable cardiac condition. (NRT has been shown to be safe in patients with stable coronary artery disease, but safety has not been adequately assessed in patients with unstable heart disease.) All patients must be willing to take NRT for up to 12 months, and be willing to complete 4 follow-up telephone-based counseling sessions and 3 follow-up visits. Although no formal assessment of psychiatric illness will be performed, subjects demonstrating markedly inappropriate affect or behavior will be excluded from the study. Everyone who attends a baseline session who is not eligible for the study but interested in quitting will be given self-help materials, such as *Clearing the Air*, and will be referred to the state tobacco quitline. They will also receive a \$20 ClinCard to compensate for their time and travel costs to attend the baseline visit.

### Randomization

All eligible participants who consent to participate in the study and complete the baseline data collection will be randomized to either SSC or LT-NRT. Randomization will be determined by computer-generated random numbers and a randomization module embedded in the data capture program.

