### Intervention

Both intervention arms will receive written smoking cessation materials and a series of 4 telephone-based counseling sessions and 1-3 in-person counseling sessions. Although the number, timing, and content of the counseling sessions will differ across the treatment arms, we anticipate that the total counseling contact time will be comparable, with one caveat. Participants in the SSC arm who are not interested in quitting within 30 days at the time of their baseline counseling session will not be offered additional counseling, which is consistent with most state quitlines. These participants will be informed that they may contact the program's hotline if they change their mind, at which point, counseling may either be reinstated or they will be referred to the state quit line for counseling. Participants in the SSC arm will receive 10 weeks of NRT contingent upon setting a quit date while participants in the LT-NRT arm will receive 52 weeks of NRT regardless of their immediate interest in quitting. An overview of the interventions is shown in Table 2.

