**Counseling-SSC.** To maximize the generalizability of the study findings, the counseling sessions for the SSC arm will emulate services provided in a typical smoking cessation program such as a state tobacco quitline. The timing, duration, and content of each counseling session will be consistent with guideline-based recommendations, and will be provided in the participants preferred language (English or Spanish). [name] will be responsible for the supervision and training on the SSC counseling protocol. [name] has extensive experience in development, training, and quality control of smoking cessation interventions, including quality monitoring for a nationwide quitline provider. Periodically, counselors will ask participants for verbal permission to audiorecord counseling sessions to demonstrate fidelity to study counseling protocols. Participants in the SSC arm will be offered up to 5 proactive counseling sessions with an in-person session at baseline and additional telephone-based sessions at weeks, 1, 3, 6 and 10 for those interested in quitting within 30 days. All counseling sessions will be delivered by a trained Tobacco Treatment Specialist. Consistent with guideline recommendations, sessions will provide basic information about smoking and successful quitting. Participants ready to set a quit date will receive practical expert support in developing a personalized plan for cessation and long-term abstinence. They will learn to recognize danger situations, develop problem-solving and coping skills, and secure social support. Counselors will encourage participants in the quit attempt, communicate caring and concern, and encourage participants to talk about the quitting process. Participants willing to set a quit date will also receive guidance on use of NRT, as outlined below. For SSC participants unwilling to make a quit attempt, the counselor will use a participant-centered approach to enhance the participant's motivation to quit as recommended in current practice guidelines. They will be informed to contact the study hotline at any time during the study, at which point they will either be referred to the state quitline or provided counseling according to the SSC protocol if still within the first 6 weeks of baseline. The participant's current tobacco-use status will guide the content of each follow-up call. If the participant is quit, the counselor will review high-risk situations, coping skills, and stress management to prevent relapse. If the participant is still smoking or has slipped, the counselor will query circumstances related to the slip and troubleshoot avoiding these situations in the future. The counselor will then use cognitive behavioral techniques to build coping skills, with the goal of helping the participant build and implement a new

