### Covariates

We will collect a variety of covariates (Table 5). These covariates will allow us to verify the comparability of the two comparison arms at baseline and will also allow us to estimate treatment effects for given personal characteristics (see discussion of CART analysis in the analytic plan). We will assess demographic variables, social history variables that might influence tobacco consumption, smoking related variables, including cpd, nicotine dependence, and biological markers of nicotine consumption, and clinical variables including both objective and subjective assessment of respiratory function and prior history of respiratory-related clinical events.

| Table 5. Co-variate measures |                                                                                                                                                                                  |
|------------------------------|----------------------------------------------------------------------------------------------------------------------------------------------------------------------------------|
| Construct                    | Measure (assessment timepoint)                                                                                                                                                   |
| Demographics                 | gender, age, race, ethnicity, income, education, employment, marital status, family structure (baseline)                                                                         |
| Social history               | Other smokers in the home, presence of home smoking restrictions, anxiety (GAD-2), depression (PHQ-2), health history (baseline)                                                 |
| Smoking Variables            |                                                                                                                                                                                  |
| Smoking history              | Quantity smoked (baseline, Mo 3, 6 & 12), quitting history, use of other tobacco and nicotine products, including e-cigs and NRT, (baseline)                                     |
| Readiness to quit            | Interest in quitting will be assessed using 30 day anchor (stage of change) and 12 months (intent to cut back or quit) (baseline, Mo 3, 6 and 12)                                |

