### Analytical Plan.

**Sample Size and Power Calculations.** Our sample size was based on our primary outcome, point-prevalence abstinence at Month 12, using an intent-to-treat approach. Based on prior studies using precessation NRT, we estimate a 2-fold increase in cessation outcomes in the LT-NRT group compared to the SSC group. Given our recruitment of patients at all levels of readiness to quit, we estimate a 12 month cessation rate of 10%. With 199 participants, in each arm, we will have an 80% power to detect a 2-fold difference or greater with a Type I error rate of 5%. This sample size will provide comparable power for looking at 6 month sustained cessation. For the CO measured longitudinally at four time points, we have 80% power to detect a mean difference of 2.24 ppm. Likewise, for NNAL, we have 80% power to detect a mean difference of 0.41 pmol/mg creatinine or more between the two groups.

**Specific Aim 1: Compare the benefits of traditional smoking cessation (SSC) versus long-term guided maintenance therapy (LT-NRT) with NRT.** The chi-square test will be used to compare the verified 7-day point prevalence abstinence at Month 12 between the two groups. If there is imbalance between treatment groups at baseline, we will switch to logistic regression for our primary analysis. We will use similar methods to test for group differences for dichotomous secondary outcomes including sustained abstinence and proportion with 1 or more ED visits or hospitalizations. To test for differences in change in respiratory symptoms and FEV1 from baseline measured at 3, 6, and 12 months, we will use standard mixed models repeated measures analysis. Likewise, to test for differences in longitudinal exposure to CO and NNAL, we will compare the area under the curve over the entire 12 months of follow-up using repeated measures analysis. If the treatment differences are heterogeneous across any covariate sub-groups, we will quantify and report such interactions

with appropriate contrast statements. We will compare the cumulative number of self-reported quit attempts by means of a Wilcoxon rank-sum test.

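### Readiness to quit is recorded before allocation and largely governs what SSC participants are offered, yet it is neither a stated stratum nor a prespecified factor in the primary analysis

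*Protocol*

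**What the plan says.** **Allocation.** Under Randomization, consenting participants who "complete the baseline data collection will be randomized to either SSC or LT-NRT", and "Randomization will be determined by computer-generated random numbers and a randomization module embedded in the data capture program". No ratio, block or stratum is given there.

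**Readiness.** The covariate table (Table 5) lists interest in quitting with a 30-day anchor among the baseline measures. It is therefore known before allocation.

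**What readiness governs.** Under Intervention, further counseling is withheld from "Participants in the SSC arm who are not interested in quitting within 30 days", judged at the baseline counseling session. NRT follows a related condition: "Participants in the SSC arm will receive 10 weeks of NRT contingent upon setting a quit date". LT-NRT participants receive 52 weeks of NRT whatever their interest. An SSC participant who later has a change of mind can use the hotline and be "provided counseling according to the SSC protocol if still within the first 6 weeks of baseline", or be referred to the state quitline.

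**Analysis.** Under Specific Aim 1 in the Analytical Plan, Month 12 verified abstinence is compared by chi-square. Then: "If there is imbalance between treatment groups at baseline, we will switch to logistic regression for our primary analysis". No threshold for imbalance and no covariates are named. The discussion of precessation treatment (Criterion 2) says that the analysis will show whether efficacy differs by readiness.

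**The concern.** Readiness does three jobs in this trial. It plausibly predicts quitting, it largely governs the treatment offered in the control arm only, and it is a subgroup of stated interest. The plan uses it neither to balance the arms nor, by default, to sharpen the primary comparison. It can enter the primary analysis only through a switch that is decided after the baseline tables are seen, against a criterion that is not written down.

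Three things are at stake: precision that could be had at no cost in participants, the even split of arms within the ready and not-ready groups, and an avoidable judgment about which analysis is primary. An analysis plan can still fix the adjustment later. It cannot restore balance once participants have been allocated.

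**Working it through.** **1. The plan's own figure.** Inputs from the power paragraph: 12-month cessation of 10%, a two-fold increase (10% against 20%), type I error 5%, power 80%. With a two-sided test and pooled variance (mean rate 0.15):

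n = [1.96 × √(2 × 0.15 × 0.85) + 0.8416 × √(0.10 × 0.90 + 0.20 × 0.80)]² / 0.10² = (0.990 + 0.421)² / 0.01 ≈ 199 per arm.

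This reproduces the stated 199; power at 199 is 80.0%. The standard error of the difference is √(0.25/199) = 3.54 points.

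**2. Chance imbalance in readiness, if allocation is simple.** The share ready, q, is not fixed by the protocol. Its introduction gives 10–20% of smokers in general; its own interviews under Criterion 4 give 7 of 21, or one-third. The between-arm difference in share ready has SD = √(q(1−q) × 2/199).

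| q | SD (points) | 95% range (points) | gap ≥ 5 points | gap ≥ 10 points |
|---|---|---|---|---|
| 10% | 3.0 | ±5.9 | 10% | 0.1% |
| 20% | 4.0 | ±7.9 | 21% | 1.3% |
| 33% | 4.7 | ±9.3 | 29% | 3.4% |
| 50% | 5.0 | ±9.8 | 32% | 4.6% |

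**3. What that does to the treatment difference.** The shift is the imbalance times the gap in quit rates between ready and not-ready smokers. The protocol gives no such gap, so ratios k of 2, 3 and 5 are assumed, with an average rate of 10%: not-ready rate = 0.10/(qk + 1 − q), ready rate = k times that. For q = 1/3 and k = 3 the rates are 6% and 18%, and 9.26 × 0.12 = 1.1 points. Over q = 10–50% and k = 2–5, the shift at the 95% extreme is 0.5 to 1.8 points. Assuming instead a gap of 15 to 25 points at one-third ready gives 9.3 × 0.15 = 1.4 to 9.3 × 0.25 = 2.3 points. Against this stand a planned effect of 10 points and a standard error of 3.54.

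**4. Error rates and power.** Simulation of 40,000 trials per setting, with q = 20%, 33%, 50%; k = 2, 3, 5; 10% average in SSC; and LT-NRT rates doubled in both readiness groups for power. The adjusted test is a Cochran-Mantel-Haenszel (CMH) test stratified by readiness.

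| Allocation | Test | Type I error | Power |
|---|---|---|---|
| Simple | Chi-square | 4.9–5.2% | 80–81% |
| Simple | Readiness-stratified CMH | 4.8–5.2% | 80.8–85.8% |
| Balanced on readiness | Chi-square | 3.8–4.7% | 81–83% |
| Balanced on readiness | Readiness-stratified CMH | 4.8–5.1% | 81.3–86.1% |

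The second row against the first shows the gain from adjustment; the fourth against the second shows the small further gain from stratified allocation. The third row shows that stratifying while keeping the unadjusted test makes that test conservative.

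**5. Arm sizes.** Simple allocation of 398 gives arms of about 179 to 219 (95%). Power at that extreme is still 79–80%, so blocking adds almost nothing to overall power.

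**The case against.** The strongest case against rests on four points.

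- *The protocol does not describe unrestricted randomization.* A reader might infer that it does. The text is silent on restriction: a module fed by computer-generated numbers is compatible with stratified permuted blocks, and the detail may sit in a document not shown. This stands, so the imbalance figures apply only if allocation is simple.
- *Chance imbalance is already covered by the 5% error rate.* This stands. A reader might infer that the chi-square is invalid or biased; the simulation shows no inflation, and the shift is smaller than one standard error.
- *Baseline readiness is not the only gate.* This stands. NRT depends on a quit date, and the hotline offers a way back, so readiness largely governs the SSC offer without deciding it alone. Nor does the protocol say that readiness is the strongest predictor of quitting.
- *Stratification is not what helps most, and is not entirely free.* Largely right. Adjustment brings most of the gain, and stratification without adjustment costs some type I error. Stratified allocation also only equalises the share ready between arms; it does not set how much control treatment is delivered overall.

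None of this answers the remaining point. The protocol does fix an unadjusted primary test with an undefined trigger for adjustment, although a suitable covariate is already collected before allocation.

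**Conclusion.** The concern holds in a modest form. No stratification or blocking is stated, and the default primary analysis leaves unused a baseline variable tied closely to the SSC treatment offer. Adjusting for it is worth up to about 6 percentage points of power at the same sample size; the gain is about 1 point if ready smokers quit at only twice the rate of others. Stratified allocation adds about half a point, with its main benefit in the readiness subgroups.

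These sizes rest on assumed quit-rate ratios of 2 to 5, on 20–50% being ready for the power figures, and on simple allocation for the imbalance figures. The stated sample size stands. This is an improvement in precision and subgroup balance; it does not call the validity of the trial into question.

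**What to change.** **Analytical Plan, Specific Aim 1.** Name the baseline survey item on readiness to quit within 30 days (yes/no) as a factor in the primary analysis, whatever imbalance is observed. A readiness-stratified CMH test stays closest to the planned chi-square; logistic regression with treatment and readiness is an alternative. Choose one in advance, and remove the switch that depends on observed imbalance.

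**Randomization.** State whether allocation is blocked and stratified. Use the same readiness item as a stratum, with permuted blocks of random size loaded into the existing module.

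In both places use the survey answer recorded and locked before allocation. The judgment made at the baseline counseling session may come after the arm is known. If stratification is adopted, the adjusted analysis should go with it.

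**Cost.** A few sentences in two sections, a new allocation table, and a check that the readiness item is complete before the module is called. No extra participants, visits or measurements are needed.
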